#### Laboratory assessment procedure

Participants and a parent will attend laboratory assessments at baseline, post-intervention (3 months after baseline), and follow-up (6 months after baseline), which consist of a battery of psychosocial, behavioral, and biomedical outcomes. The hour-long assessments will be conducted in the Physical Activity and Nutrition Clinical Research Consortium Laboratory at Kansas State University by a team of two trained graduate research assistants. The assessments will include (1) demographic and parent dietary/physical activity information, (2) quality of life questionnaire, (3) self-efficacy and enjoyment of physical activity/fruit and vegetable questionnaire, (4) child dietary intake questionnaire, (5) physical activity levels via accelerometry over a 5-day period, (6) anthropometric assessments, (7) blood pressure, (8) pulmonary function measurements, and (9) markers of systemic inflammation. The details and specific methodology for each component of the assessment follow. Following the baseline assessment period, the 12 weeks of home-based wellness visits will begin.

#### Laboratory measures

##### Demographic and parent information

Previously validated questionnaires will be used to assess parental demographics, physical activity levels [31], and fruit and vegetable consumption [32].

##### Psychological outcomes: child quality of life, self-efficacy, and enjoyment

In order to assess quality of life, the PedsQL instrument for ages 8 through 12 and the PedsQL parent-proxy report for ages 8 through 12 will be used. The PedsQL has been shown to be reliable and valid in the core quality of life areas (physical, emotional, social, school) for a pediatric population, and it is appropriate for use in clinical trials [33]. Additional self-report instruments will be used to assess participant (child) self-efficacy [34] and enjoyment [35] for physical activity and will be modified additionally to assess these constructs for fruit and vegetable consumption. Should questions or difficulties arise when girls are completing the questionnaires, research staff will provide clarification and assistance as needed.

##### Behavioral outcomes: child typical dietary intake

Together with their parent or caregiver, the girls will complete the Childhood Dietary Questionnaire [36]. The participants will be asked to report the number of times that they have consumed particular foods in the past 24 h or 7 days, depending upon the food category, in accordance with standard instructions and the format of the dietary questionnaire. The Childhood Dietary Questionnaire will be used to assess dietary intake and is a validated tool to measure intake in the categories of fruits and vegetables, dairy fat, sweetened beverages, and non-core foods. This questionnaire is not meant to assess caloric intake but rather intake in specific categories of diet over a specified time period. From this questionnaire, we will be able to assess fruit and vegetable consumption by determining the number of types and various categories of these foods that the participants consumed.

##### Behavioral outcomes: physical activity

Actical physical activity monitors (Respironics Inc., Bend, OR, USA) will be used to measure the physical activity behaviors of the participants. These are small pedometer-like devices that can be worn on the wrist. Participants will wear an Actical accelerometer on their non-dominant wrist for seven continuous days at each assessment period. The research assistant will apply a locking nylon band to secure the device to each girl’s wrist, ensuring continual wear. The accelerometers will be initialized to record data in 15-s epochs. After 1 week of wear, participants will return to the laboratory to have their wrist band removed, and the data will be downloaded and analyzed. Upon data download and analysis, device location will be specified as wrist, and the default adolescent Actical software cut points of 0.01 kcal/min/kg (sedentary/light), 0.04 kcal/min/kg (light/moderate), and 0.10 kcal/min/kg (moderate/vigorous) will be used. After the participant has worn the device, the data can be downloaded for an analysis of daily information regarding total steps, total time, and percentage of time spent engaged in sedentary, light, moderate, and vigorous physical activities.

##### Biomedical outcomes: anthropometrics

For all body composition assessments, participants will be asked to remove their shoes and any outer clothing or heavy garments. The research assistant taking measurements will be the same for all assessment periods and for all participants. Height will be measured to the nearest 0.1 cm with a portable stadiometer (Invicta Plastics, Leicester, England), and weight will be measured to the nearest 0.1 kg with a digital scale (Pelstar LLC, Alsip, IL, USA). BMI will be calculated as weight (kg) divided by height (m) squared and then converted to age-sex percentiles via CDC growth charts [37]. Waist circumference will be measured via a non-elastic Gulick tape measure in the horizontal plane at the iliac crest following a normal exhalation. All anthropometric measurements will be taken in duplicate, and a third measurement will be recorded if the values differ by more than 0.5 cm or 0.5 kg. The two values that are within the acceptable difference range will then be averaged and subsequently used in analyses.

A dual-energy x-ray absorptiometry (DEXA) scan will be performed to assess body composition, and relevant information will be collected, including fat, lean, and bone tissue content (GE Lunar Prodigy, Madison, WI, USA). Participants will be asked to remove heavy outer clothing, everything from their pockets, and any metal jewelry before they lie down on top of the x-ray bed. During the approximately 5-min scan, participants will be instructed to lie as still as possible. Additionally, bioelectrical impedance analysis (RJL Systems, Quantum II, Clinton Twp, MI, USA) will be performed to determine the amount of body water and resulting body composition of participants. The top of the right hand and foot will be cleaned with an alcohol swab, and the area will be given time to dry. An electrode tab will be placed in one of four specified locations on the same side of the body: around the proximal portion of the middle finger, across the top of the wrist, across the top of the ankle, and on the joint between the metatarsal phalanges on the top of the foot. The BIA wires will be connected to the electrode tabs, and readings will be recorded for both resistance and reactance. These values will be entered into the prediction equation using RJL software to calculate body composition.

##### Biomedical outcomes: blood pressure

Blood pressure will be measured with an automated blood pressure device (Omron Healthcare, model HEM-907XL, Vernon Hills, IL, USA) to obtain measurements for systolic and diastolic blood pressure, as well as pulse rate. A research assistant will measure blood pressure in a quiet room while the participant is in a seated position with both feet resting on the floor. The appropriate-sized blood pressure cuff will be applied to the upper left arm, so that the bottom of the cuff is approximately 1 in. above the elbow crease. Participants will be instructed to remain relaxed and still during the measurement. There will be at least 1 min between blood pressure measurements. Blood pressure assessments will be taken in duplicate, and a third measurement will be taken if the values for systolic or diastolic recordings differ by more than 5 mmHg.

##### Biomedical outcomes: pulmonary function

Pulmonary function will be assessed via a handheld spirometer and disposable mouthpiece (MIR winspiroPRO, version 4.4.1, Waukesha, WI). Pulmonary function outcomes of interest will include peak values of forced vital capacity (FVC) (L), forced expiratory volume over FVC (FEV1/FVC), and forced expiratory flow volume in 1 s (FEV_1_, L/s), and values will be compared to norms for age, height, ethnicity, and sex. For the measurement of lung capacity and functionality, participants will hold the spirometer while in a seated position with feet flat on the floor with their back supported and straight. The participants will wear a noseclip to ensure that all expired air is collected through the mouthpiece. PFTs will be performed, according to the American Thoracic Society criteria [38], twice, and a third measurement will be taken if FVC differs by more than 150 mL between measurements.

##### Biomedical outcomes: systemic inflammation

A marker of systemic inflammation, C-reactive protein, will be assessed via a passive drool sample. Prior to collection of the passive drool sample, participants will be asked to rinse their mouth thoroughly with water. Saliva will be collected using the Saliva Collection Aid (Salimetrics, item no. 5016.02) into a polypropylene vial (Salimetrics, item no. 5002.02). Participants will be instructed to provide approximately 1.0 mL in a 2.0-mL cryovial through the passive drool process. We will store the collected samples in a sub-60 °C freezer for storage until processing and analysis takes place. The thawed samples will be processed using enzyme-linked immune sorbent assay (ELISA) (MyBioSourceMBS163178). In our previous work, intra-assay precision was coefficient of variation (CV) < 10 % and inter-assay precision was CV < 12 %. Sensitivity of the assay was 0.01 mg/L. On the day of the assay, the samples will be thawed, vortexed, and centrifuged at 1500×*g* (at 3000 rpm) for 15 min to remove mucins and other particulate matter.

### Cost-effectiveness evaluation

Over the course of the intervention, we will calculate monetary and time costs required for delivering the intervention components and performing laboratory assessments. This will inform future estimates of cost-effectiveness for a larger-scale intervention.

### Statistical analyses

Feasibility outcomes (retention, participation, compliance, etc.) will be assessed through descriptive statistics. Data will be analyzed using SPSS statistical software (version 22.0). Despite a lack of power to detect differences between the two intervention arms, we will perform a preliminary assessment of change in psychosocial, behavioral, and biomedical outcomes. There will be an emphasis on presenting the descriptive statistics for health-related outcomes, with summary statistics and confidence intervals reported. An alpha of 0.05 will be used for all analyses, and effect sizes for future sample size calculations will be calculated on potential primary outcome measures by subtracting baseline means from post-intervention and follow-up means, divided by the appropriate pooled standard deviation. Where appropriate, results will be presented as point estimates, supported by 95 % confidence intervals.

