## Methods/design

### Study design

As shown in Fig. 1, this study is a two-arm, parallel randomized trial comparing two home-based coaching interventions on primary feasibility outcomes related to recruitment, intervention delivery and acceptance, and health outcome assessments, with secondary, preliminary measures related to health-related psychosocial, behavioral, and biomedical outcomes of female children. The home-based, wellness coaching intervention period will last for 12 weeks, with laboratory assessments at baseline, post-intervention (3 months after baseline), and at follow-up (6 months after baseline). A 6-month follow-up period was chosen to evaluate the feasibility of having participants return to the laboratory for an assessment following the conclusion of the intervention. A fully powered study examining the impact on health outcomes may employ a longer-term follow-up to assess maintenance of behavior change and subsequent changes in health outcomes.

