### Study population

Participants for this study are 40 females aged 8 to 13 years. All girls will have a body mass index (BMI) at or above the 85th percentile (overweight or obese) of gender-specific, age-adjusted growth charts and must reside within 20 miles of Manhattan, KS (Kansas State University). Exclusion criteria require that the girls do not have developmental delays, psychiatric problems, or any illness, injury, or condition that prevents them from participating in moderate-to-vigorous physical activity. Finally, the participants cannot be taking weight-altering medication or be participating in any other weight control program. There will be no inclusion/exclusion criteria related to socioeconomic status or ethnicity. Parental consent and child assent will be obtained from all participants prior to their participation in the study. Kansas State University Institutional Board of Human Ethics approval has been obtained, and all study methods will comply with the Declaration of Helsinki.

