### Randomization

Rolling recruitment will be implemented, and participants meeting the inclusion criteria will be block-randomized using an online randomization program into one of two wellness coaching conditions, in blocks of four, with a 1:1 allocation ratio. The principal investigator will oversee the randomization process and will keep allocation concealed until baseline assessments have been completed. Research assistants collecting assessment data will be blinded to group randomization over the course of the study. Blinding of the study participants to their group assignment will not be possible due to the nature of the intervention itself, but participants will not know their assigned condition until after baseline assessments.

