### Secondary outcome evaluation

The health-related psychosocial outcomes include changes in child quality of life (measured through the PedsQL instrument), as well as self-efficacy and enjoyment of physical activity and fruits and vegetables. Health-related behavioral outcomes for this study are the change in daily physical activity and sedentary time (minutes per day, as measured by accelerometer), steps per day, and fruit and vegetable intake. Health-related biomedical outcomes include change in BMI *Z*-score from baseline, as well as changes in body fat percentage, waist circumference, blood pressure, pulmonary function, and systemic inflammation.

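### A 0.05 significance threshold for all analyses, and pre-post effect sizes for planning, do not fit a trial that is admittedly underpowered and meant to be descriptive

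*Protocol article*

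**What the plan says.** All the relevant statements about analysis stand in one paragraph, Statistical analyses.

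- **Power:** "Despite a lack of power to detect differences between the two intervention arms, we will perform a preliminary assessment of change" in the health-related outcomes.
- **Presentation:** the emphasis is on descriptive statistics, and where appropriate "results will be presented as point estimates, supported by 95 % confidence intervals".
- **Threshold:** "An alpha of 0.05 will be used for all analyses". Health outcomes are not exempted, and any tests on them are not labelled exploratory.
- **Planning values:** the sentence with the threshold goes on to define effect sizes for future sample size calculations. Each is the post-intervention or follow-up mean minus the baseline mean, over a pooled SD. They are to be computed on possible primary outcomes, in the plural and without names.

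The Discussion says that no published effect sizes exist for this type of intervention and that the preliminary results will inform a fully powered trial. It makes that trial conditional on feasibility.

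The outcome list is long. Secondary outcome evaluation names quality of life, self-efficacy, enjoyment, four behavioral measures and BMI Z-score, "as well as changes in body fat percentage, waist circumference, blood pressure, pulmonary function, and systemic inflammation". All are measured again at 3 and 6 months.

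**The concern.** A significance threshold is a decision rule. In a between-arm comparison declared to lack power, crossing it is weak evidence and failing to cross it is uninformative, so it serves no purpose that the article states. It can still do harm, because this trial is the stated source of planning values, the candidate primary outcomes are open, and 0.05 is the only cut-off given for health outcomes. If the next trial's outcome or effect size were picked because a result crossed 0.05, the planning effect would be too large and the next trial too small.

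The planning effect size has a separate weakness. A pre-post mean change within an arm contains everything that happens to growing girls over 3 to 6 months, as well as regression to the mean in a sample enrolled at or above the 85th BMI percentile. A randomized two-arm follow-on trial is sized on the difference between arms, and the planned calculation does not give that quantity.

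**Working it through.** The article states no power figure or error rate to reproduce. The check asks what the 0.05 threshold implies at this sample size.

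**Inputs from the article.** Sample size: "Participants for this study are 40 females aged 8 to 13 years" (Study population). Allocation: "in blocks of four, with a 1:1 allocation ratio" (Randomization), hence 20 per arm. Alpha is 0.05, taken as two-sided to match the 95% intervals. There are two post-baseline visits.

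**Assumptions.** True standardized differences of 0.3 and 0.5, because the article gives none. A two-sample t-test at each visit, because the article names no test. No dropout, except where 16 per arm is shown.

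**1. Number of outcomes (my count).**
- Counting by heading: psychosocial 5 (quality of life; self-efficacy for activity and for fruit and vegetables; enjoyment of each), behavioral 4, biomedical 6. Total 15.
- Adding the parent-proxy quality-of-life report (+1) and splitting blood pressure into 2 (+1) and pulmonary function into 3 (+2): 6 + 4 + 9 = 19.
- Over two visits this makes 30 to 38 possible between-arm comparisons.

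**2. Chance findings if each were tested at 0.05 and no effect existed.**
- Expected number: 30 × 0.05 = 1.5; 38 × 0.05 = 1.9.
- At least one, if independent: 1 − 0.95^30 = 78.5%; 1 − 0.95^38 = 85.8%.
- The outcomes are clearly correlated. Simulation of 38 equicorrelated tests gives about 73%, 56% and 37% at correlations of 0.3, 0.5 and 0.7.

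**3. Smallest observed d that can reach p<0.05.**
- d_min = t(0.975; 2n − 2) × √(2/n).
- n = 20: 2.024 × √0.1 = 0.64. With 16 per arm it is 0.72.

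**4. Power and exaggeration at 20 per arm** (noncentral t for power, simulation for the means).

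| True d | Power | Mean estimated d, all results | Mean absolute d, significant results | Ratio to truth |
|---|---|---|---|---|
| 0.3 | 15% | 0.31 | 0.82 | 2.7 |
| 0.5 | 34% | 0.51 | 0.87 | 1.7 |

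The third column matters: without selection the estimate is nearly unbiased. The exaggeration comes entirely from choosing on significance.

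**5. Consequence for the next trial if selection occurred.**
- n per arm = 2 × (1.96 + 0.84)² / d², at 80% power.
- d = 0.85 (a typical significant estimate): 22. d = 0.5: 63. d = 0.3: 175.

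**6. Which effect size a two-arm trial needs.**
- The planned quantity is, within an arm, (later mean − baseline mean)/SD.
- The quantity needed is (HEPA − HE)/SD at the later visit. The two agree only if the HE arm does not change, yet HE is an active coaching arm.
- Adjusting for baseline is also more precise than comparing change scores. With baseline-to-follow-up correlation ρ, the variances stand as (1 − ρ²) to 2(1 − ρ), a ratio of (1 + ρ)/2. At assumed ρ of 0.5 and 0.7 this is 0.75 and 0.85, so 25% and 15% less variance.

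**The case against.** The strongest reply is that the harmful step is not in the plan. No passage lets a p-value select an outcome, an arm or an effect size. The planning effect sizes are not conditional on significance, and progression depends on feasibility. This stands. A reader might infer that the alpha sentence makes significance the selector of the next trial's primary outcome, or that 38 between-arm tests are planned. The documents support neither: they name no test and no number of tests, and the effect size they define is a change from baseline.

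Second, the same paragraph already stresses description and 95% intervals and discloses the lack of power. This also stands, and part of the remedy is therefore already planned. But an emphasis on description does not cancel a threshold applied to every analysis.

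Third, unadjusted 95% intervals exclude zero exactly as often as tests at 0.05 reject. That is correct, so deleting the alpha statement would not by itself remove chance findings. Naming the candidate outcomes beforehand is what guards against selection.

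Fourth, the absence of multiplicity control for preliminary outcomes in a feasibility trial is not an error. I agree, and no adjustment is asked for.

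Fifth, the Discussion wants to see change in each arm, so a pre-post effect size may be deliberate. As description it is reasonable. As the basis for sizing a randomized comparison it is the wrong quantity.

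**Conclusion.** The point holds in a limited form. The paragraph combines an admitted lack of between-arm power and a descriptive aim with a blanket 0.05 threshold, and it draws planning effect sizes from pre-post changes on unnamed outcomes. These do not fit together.

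The size of the risk is conditional. If a choice were made on significance, a modest effect would be overstated about 1.7-fold at a true d of 0.5 and 2.7-fold at 0.3, because nothing below an observed d of 0.64 can qualify. If no such choice is made, that bias does not arise. The figures rest on assumed effects, a two-sample t-test and 20 analysed per arm; dropout would raise the bar. The outcome count of 15 to 19 depends on how composites are split, and the 78.5% and 85.8% chances of a false positive are upper-end values because they assume independence.

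The mismatch between pre-post and between-arm effect sizes does not depend on those assumptions. It requires only that the follow-on trial compares randomized arms, which the Discussion says it will.

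**What to change.** For the health outcomes, replace the alpha statement with estimation only. For each outcome and visit, report the baseline-adjusted HEPA-HE difference with its 95% confidence interval, label it exploratory, and do not describe it as significant or not significant. Within-arm changes can still be shown descriptively.

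Name the candidate primary outcomes for the next trial before the data are seen. Base its planning on the between-arm intervals and the outcome SDs for those candidates, not on pre-post effect sizes or on whichever results cross 0.05. The intervals will be wide: at 20 per arm the half-width is about 1.96 × √(2/20) = 0.62 SD.

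The cost is a small change in the analysis, using data already to be collected, and giving up any formal efficacy statement from this trial.

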## Background

Approximately one out of every three children in the USA is overweight or obese [1]. Obese children are more likely than healthy weight children to have detrimental health outcomes, including high blood pressure, dyslipidemia, type 2 diabetes, and psychosocial problems [2–4]. Additionally, overweight and obese children are at a significantly greater risk of adult obesity, compared to children at a healthy weight [5]. This tracking of obesity into adulthood may lead to the development of more severe health outcomes [6]. In addition to health problems related to obesity, there is considerable financial burden associated with childhood obesity; medical costs from youth into adulthood are estimated at approximately $19,000 more per obese child, in comparison with healthy weight children [7]. As such, early interventions that target obesity treatment and prevention are warranted.

Successful childhood obesity interventions aim to regulate body fat and weight, while allowing for further growth [8] in ways that promote the persistence of healthful behaviors throughout the developmental years [9]. The goal is typically not weight loss but rather to achieve increases in height while slowing weight gain. Secondary prevention measures may focus on reducing the impact of childhood obesity by slowing or reversing the weight gain through the building of healthful behaviors. Secondary prevention techniques may include self-efficacy and skill-building for behaviors related to nutrition and physical activity [10]. Given that obesity may result from prolonged positive energy imbalance, interventions typically promote increased energy expenditure or appropriately balanced caloric intake, which can each be considered independent avenues to improve obesity outcomes. It is critical that childhood obesity interventions are handled with “kid gloves,” in that great care is taken to not stigmatize the individuals, and to ensure that quality of life is considered alongside weight status and healthful behaviors.

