## Discussion

With the results from this study, we will determine whether or not a home-based wellness coaching program is feasible for use with female children. A secondary outcome will be to evaluate the possibility of change in health-related psychosocial, behavioral, and biomedical outcomes through each intervention condition. Since this is a feasibility trial, we want to assess outcomes for both of the treatment arms of the intervention. The intervention conditions will be evaluated for future potential, so that they may be integrated most effectively into a future fully powered randomized controlled trial. For this type of intervention, we will recruit participants through the parents, who are concerned, at least to some extent, with the health of their children. As such, it may not be an ethical or viable option to offer no type of intervention. Because of this, our active comparison group represents general health behavior mentoring but does not focus specifically on physical activity and nutrition. This condition of health behavior mentoring used in our active comparison group, while not precisely current practice, represents more of a “standard” than the hands-on approach used in the HEPA intervention arm. Since this is a new combination of a one-on-one wellness coaching intervention delivered within the home setting to girls, there is no current literature available regarding effect sizes needed for future power calculations. As such, we will assess the preliminary impact on health-related outcomes to more appropriately inform a future fully powered trial. Using a 6-month follow-up assessment will allow us to evaluate the feasibility of having participants return to the laboratory following a no-contact period, as well as the potential for lasting impacts resulting from the study.

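### The effect sizes intended for sizing a future randomized trial are defined as change from baseline, not as the HEPA-minus-HE difference, so that trial could be mis-sized in either direction

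*Protocol article*

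**What the plan says.** The Statistical analyses section gives both a purpose and a formula. The purpose: "effect sizes for future sample size calculations will be calculated on potential primary outcome measures". The formula: "by subtracting baseline means from post-intervention and follow-up means, divided by the appropriate pooled standard deviation". No subtraction of one arm's change from the other's appears.

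The Discussion explains why these figures are wanted. It says that no published effect sizes exist for this type of intervention and that "we will assess the preliminary impact on health-related outcomes to more appropriately inform a future fully powered trial". It also speaks of evaluating change within each condition, which fits a pre-post reading of the formula.

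The trial itself is a two-arm parallel comparison randomized 1:1, with 40 girls in total (Study design, Study population, Randomization). The HE arm is described as an active comparison group. It receives the same 12 weekly visits, with goal-setting, self-monitoring and education that includes physical activity (Background; Wellness coaching interventions).

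**The concern.** The stated quantity does not fit its stated use. The sample size of a randomized comparison depends on how far the arms differ at follow-up, given baseline. Change from baseline in one arm contains any effect of that arm's intervention, mixed with whatever would have moved the outcome anyway and whatever the comparator also achieves. The article itself gives reasons to expect such shared movement:

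- **Active comparator.** HE coaching may improve the same outcomes.
- **Growth.** The girls are 8 to 13, and the Background says that successful programmes "aim to regulate body fat and weight, while allowing for further growth". Over 3 to 6 months this matters for outcomes that are not age-standardised, such as waist circumference and blood pressure.
- **Season.** Recruitment is rolling and each girl's interval covers 3 to 6 calendar months, so activity and diet may shift with the time of year.
- **Regression to the mean.** Every girl is selected for a BMI at or above the 85th percentile.

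Because the Discussion says there is no other source of effect sizes, a figure from this formula could be carried straight into the next trial's power calculation.

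**Working it through.** **Plan's own figure.** The sample of 40 is a recruitment target with no effect size, SD or power attached, so there is no power calculation to reproduce. As a consistency check, the between-arm effect detectable with 80% power at 20 per arm (two-sided 5%) is (1.960 + 0.842) × √(2/20) = 0.89 SD. That agrees with the article's own words, "Despite a lack of power to detect differences between the two intervention arms".

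**Inputs.** From the article: alpha 0.05, 1:1 allocation, and the formula. Assumed, because the article gives none: a two-sided test, 80% power, and the size of the changes. All effects are in units of one common SD.

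**Formulas.** Write the mean changes as D(HEPA) and D(HE).
- Effect as the plan defines it, for HEPA: D(HEPA).
- Effect that sizes a HEPA-versus-HE comparison: D(HEPA) − D(HE).
- n per arm = 2 × (1.960 + 0.842)² / d², rounded up.
- Power at n per arm = Φ(d × √(n/2) − 1.960).

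**Main illustration, D(HEPA) = 0.5.** The rule as written gives 2 × 7.85 / 0.25 = 62.8, so 63 per arm.

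| HE change as share of HEPA change | Between-arm d | Needed per arm | Power with 63 per arm |
|---|---|---|---|
| 0 | 0.5 | 63 | 80% |
| 25% | 0.375 | 112 | 56% |
| 50% | 0.25 | 252 | 29% |
| 75% | 0.125 | 1,005 | 10% |

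The middle case in numbers: 2 × 7.85 / 0.0625 = 251.2, so 252 per arm. Power with 63 is Φ(0.25 × √31.5 − 1.960) = Φ(−0.557) = 29%.

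**Other assumed starting points.** For HE shares of 25%, 50% and 75%, a pre-post d of 0.3 gives 175 per arm where 311, 698 or 2,791 are needed. A pre-post d of 0.8 gives 25 where 44, 99 or 393 are needed.

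**Opposite direction.** If HEPA changes by +0.3 and HE by −0.2, the rule gives 175 per arm. The between-arm effect is 0.5 and needs only 63.

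**No arm difference at all.** A simulation with 20 per arm, 20,000 runs, an assumed pre-post correlation of 0.8 and a shift of 0.5 SD common to both arms gave an average pre-post effect of 0.52 and an average between-arm effect of 0.00. The planned metric can thus return a moderate effect where the arms do not differ.

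**Denominator.** The article says "divided by the appropriate pooled standard deviation" without saying whether pooling is over arms or over time points. The unit matters: with the raw SD set to 1, the SD of change is √(2(1 − r)), which is 1.00, 0.77 or 0.45 at assumed correlations of 0.5, 0.7 or 0.9.

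**The case against.** **A condensed article may leave details to an analysis plan.** The model, the covariates and the exact pooled SD are normal content for a plan that is not shown, and nothing forbids differencing the per-arm changes later. This covers the detail but not the formula. The article states a numerator and its use, and the two do not match.

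**The future comparison is not stated.** The article says only that a fully powered randomized controlled trial may follow. HEPA versus HE is an inference, though the Discussion's doubt about offering no intervention makes it plausible. The point does not depend on it: with any other comparator, the pre-post effect is right only if that comparator shows no change.

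**Growth is partly handled already.** This stands. BMI is analysed as a Z-score, and pulmonary values are to be compared with norms for age, height, ethnicity and sex. Growth is a concern mainly for waist circumference and blood pressure, and for raw lung volumes if those are analysed. The size of regression to the mean is unknown, and it would be small for a measure with high repeat correlation.

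**Baseline adjustment lowers the required numbers.** True, but it multiplies both requirements by (1 − r²), so their ratio is unchanged if both are calculated in the same way.

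**Stronger readings.** A reader might infer that the planned effect sizes capture only time effects. They do not; any intervention effect is in them too, mixed with the rest. A reader might also infer that the overall 0.05 level and the several candidate outcomes amount to a plan to pick the largest effect. The article does not say so. It admits the lack of power, emphasises descriptive statistics and promises 95% confidence intervals.

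**Conclusion.** The stated effect-size rule is wrong for its stated use and should be corrected. As written it yields a pre-post change, which matches the between-arm effect only if the comparator does not change, and an active HE arm gives no ground to assume that.

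The direction of the error is not fixed. The next trial would usually be too small if both arms improve and too large if HE worsens. The size depends on assumed inputs: since n varies with 1/d², a between-arm effect half the pre-post effect needs four times the sample (252 against 63 per arm). A reader might want one definite inflation factor or the conclusion that the future trial will be underpowered. The article gives no effects or SDs to support either.

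The reach is limited. Recruitment, delivery, fidelity, satisfaction, adverse effects and assessment completion are the primary outcomes, and none is touched. It would go too far to say that the trial's main product is compromised. What is affected is the secondary aim of informing the next trial.

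**What to change.** Replace the effect-size sentence in Statistical analyses with a rule along these lines:

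- For each candidate primary outcome, at post-intervention and at follow-up, the effect size is the HEPA-minus-HE difference adjusted for that outcome's baseline value, divided by a named SD (for example the baseline SD pooled over arms), with its 95% confidence interval.
- The SD and the baseline-to-follow-up correlation are reported alongside, for use in planning.
- Change within each arm is reported as description only and is not used to size a future trial.

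The cost is the rewording of one paragraph. Randomization and the planned assessments already supply the data. The downside is small: the between-arm estimates will usually be smaller than the pre-post ones, and their intervals wide. At 20 per arm an observed d of 0.5 has an approximate 95% interval of 0.5 ± 1.96 × √(2/20 + 0.5²/80), that is −0.13 to 1.13. That width shows how little 40 girls can say about the effect, and it is why the SD and correlation are worth reporting as planning inputs.
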